### Statistical analysis

Descriptive statistics will express continuous variables as means (±standard deviation) or medians (interquartile range) and categorical variables as proportions. Chi-square tests or Fisher’s exact tests, along with Student’s *t*-tests or Wilcoxon rank-sum tests, will be used to compare demographics and clinical characteristics between cases and controls. Chi-square tests will compare dichotomous outcomes, while *t*-tests or Mann-Whitney *U*-tests will compare quantitative outcomes. Kaplan-Meier curves and log-rank tests will evaluate survival analyses, with Cox proportional hazard models calculating hazard ratios and 95% confidence intervals (CIs). Multivariate logistic regression will identify independent predictors, and linear or generalized linear models will assess the impact of ASPP and other factors on delivery outcomes and the ASQ-3 results. First, logistic regression will calculate odds ratios and 95% CIs for recurrent stroke. Subgroup analysis will evaluate potential differences in endpoints for predefined subgroups (such as gestational hypertension, preeclampsia, HELLP syndrome, gestational diabetes, trimester, and type of delivery). Multiple imputation will address missing baseline data, with a *p*-value of < 0.05 considered statistically significant.

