**Fig. 1 Fig1:**
[figure not shown]
The geographical distribution of centers participating in the ASPP study. The ASPP study aims to include 36 territorial or regional centers across 22 provinces in China

ASPP patients and non-ASPP participants from January 2015 to November 2024 will be included (Fig. 2). Table 1 lists the inclusion criteria and exclusion criteria. ASPP patients are defined as those who experience acute stroke events during pregnancy or within 6 weeks postpartum, confirmed by neuroimaging evidence of cerebral infarction or hemorrhage corresponding to their symptoms.

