Grouping of non-ASPP participants is as follows:Non-ASPP participants include two matched control groups: The first group consists of participants in the pregnancy or postpartum period without a history of stroke (pregnancy/postpartum non-stroke group); the second group consists of nonpregnant or non-postpartum participants who have recently experienced a stroke (nonpregnant stroke group).Matching criteriaFor the pregnancy/postpartum non-stroke group, controls will be matched to ASPP cases in a 1:1 ratio based on age (±2 years) and hypertension history, with the latter stratified into preexisting hypertension, pregnancy-induced hypertension, or no hypertension.For the nonpregnant stroke group, a 1:1 matching strategy will be applied using age (±2 years), stroke etiology (classified by TOAST criteria), and preexisting hypertension status.Classification of pregnancy-related etiologies is as follows:Postpartum vascular diseasePregnancy-related hypercoagulable statesPregnancy-induced hypertensionPreeclampsiaAmniotic fluid embolismMatching of nonpregnant/postpartum patientsAge matching (±2 years)Matching based on stroke etiology, such as cardiogenic stroke, atherosclerotic stroke, small vessel disease stroke, and other identifiable causes (e.g., intracerebral hemorrhage)Health status and comorbidities, including common comorbidities such as cardiovascular disease, hypertension, and diabetesLifestyle factors, such as smoking and alcohol consumption historyDiscussion of the impact of pregnancy-related etiologiesEtiological characteristics, such as thrombosis resulting from pregnancy-related hypercoagulable states, hemodynamic changes caused by postpartum vascular disease, and hypertensive lesions associated with preeclampsiaPhysiological changes: Physiological changes during pregnancy, such as increased blood volume, blood pressure fluctuations, and alterations in coagulation mechanismsPsychological and social factors: Assessing the unique challenges faced by pregnant women in coping with stress, anxiety, and other mental health issues, as well as their potential impact on stroke occurrenceImpact assessment: When comparing ASPP patients with nonpregnant stroke patients, the influence of pregnancy-related etiologies on stroke recurrence rates and long-term prognosis will be clearly delineated.

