### Follow-up schedule

All participants will be followed up through telephone interviews. The initial follow-up is scheduled to take place between December 2024 and February 2025. The follow-up phase will consist of three rounds, each lasting 3 months and conducted every 3 years. The specific follow-up schedule is as follows:(1) First follow-up: Conducted between December 2024 and February 2025, focusing on stroke recurrence, cardiovascular health indicators, and quality-of-life assessments. During this period, any newly occurring stroke events will be documented, including the nature and severity of recurrent strokes, and changes in cardiovascular risk factors, such as blood pressure and lipid levels, will be monitored.(2) Second follow-up: Conducted between December 2027 and February 2028, continuing with telephone interviews and standardized questionnaires to assess participants’ life quality, including emotional state and daily activity capacity, while monitoring stroke and cardiovascular health status(3) Third follow-up: Conducted between December 2030 and February 2031 to further observe late-stage stroke and cardiovascular disease, particularly focusing on the increased cardiovascular risk phase post-menopause.

If participants report a stroke recurrence during the follow-up period, researchers will obtain the hospitalization records through the following process to confirm the event: First, researchers will contact the participant’s attending physician or the relevant hospital to systematically request the hospitalization records and medical information. Second, relevant medical records will be reviewed to verify the reported recurrence event, including confirmation of diagnosis, treatment course, and length of hospitalization. Additionally, if necessary, researchers will request neuroimaging assessments (such as CT or MRI) to further confirm the nature and severity of the stroke.

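### Recurrent stroke is assigned a logistic odds ratio despite follow-up from about 1 day to 10.2 years, Cox is tied to no endpoint, and no method for the 1:1 matching is named

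*Protocol article*

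**What the plan says.** All references are to the protocol article.

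- **Design and Primary outcome.** Aim 2 is a cohort study of the effect of ASPP on recurrent stroke. Its primary outcome is recurrent stroke confirmed by neuroimaging.
- **Statistical analysis, recurrence.** The one sentence that gives this outcome a method is "First, logistic regression will calculate odds ratios and 95% CIs for recurrent stroke". It states no time horizon, offset or time term. It opens as the first of several steps, but no second step follows.
- **Statistical analysis, time-to-event.** Shortly before that sentence: "Kaplan-Meier curves and log-rank tests will evaluate survival analyses, with Cox proportional hazard models calculating hazard ratios". No endpoint is named.
- **Calendar.** "ASPP patients and non-ASPP participants from January 2015 to November 2024 will be included" (Participating centers and patient population). "First follow-up: Conducted between December 2024 and February 2025" (Follow-up schedule). Later rounds end in February 2031.
- **Matching (same section as the inclusion window, after Table 1).** For the pregnancy/postpartum non-stroke group, "controls will be matched to ASPP cases in a 1:1 ratio" on age and hypertension history. The nonpregnant stroke group is matched 1:1 on age, TOAST etiology and preexisting hypertension. A further list in that section adds comorbidities and lifestyle. Index date appears in neither.
- **Tests named.** Chi-square, Fisher, t and Wilcoxon rank-sum tests "will be used to compare demographics and clinical characteristics between cases and controls". For outcomes, "Chi-square tests will compare dichotomous outcomes", with t or Mann-Whitney tests for quantitative ones. For risk and prognostic factors, "Multivariate logistic regression will identify independent predictors". No paired or conditional method is named.

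**The concern.** An ever/never odds ratio counts a woman called days after her stroke and a woman called ten years after hers as equally exposed to recurrence. If ASPP patients and their comparators have different distributions of index date, that difference enters the OR as though it were an effect of ASPP. The design does not make the distributions alike, because controls are not matched on index date and the nonpregnant group is described as having had a recent stroke. The Aim 1 primary outcome (mRS or EQ-5D at follow-up) shares the difficulty, since it is measured at no fixed time after the stroke.

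Naming Cox regression without an endpoint does not remove the problem. With both an OR and an HR available for the Aim 2 primary outcome, the choice between them could be made after the results are seen.

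The second issue is the matching. In a matched case-control comparison, an analysis that ignores the matching factors tends to pull the OR towards 1 when exposure varies with them. In a matched cohort, ignoring the pairs mainly makes the standard errors wrong.

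**Working it through.** **1. Range of follow-up (dates from the article).**
- Shortest at round 1: 30 November 2024 to 1 December 2024 = 1 day.
- Longest at round 1: 1 January 2015 to 28 February 2025 = 3,711 days; 3,711 / 365.25 = 10.16 years.
- Longest at round 3: 1 January 2015 to 28 February 2031 = 16.16 years.

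**2. Logistic OR when the true recurrence rates are equal.** The article gives no recurrence rate, so 2% per year (constant, both groups) is an assumption, as are the follow-up lengths. Risk by time T is 1 − exp(−0.02T), so the odds are exp(0.02T) − 1.
- T = 4: exp(0.08) − 1 = 0.0833 (risk 7.7%)
- T = 5: exp(0.10) − 1 = 0.1052 (risk 9.5%)
- T = 6: exp(0.12) − 1 = 0.1275 (risk 11.3%)

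| ASPP vs control follow-up (years) | OR (true HR 1) |
|---|---|
| 4 vs 6 | 0.0833 / 0.1275 = 0.65 |
| 5 vs 6 | 0.1052 / 0.1275 = 0.82 |
| equal | 1.00 |
| 6 vs 4 | 0.1275 / 0.0833 = 1.53 |

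**3. Simulation of the same point.** 400 versus 400 women, 400 replicates, assumed constant control hazard of 2% per year, follow-up uniform from near zero up to the limit shown. Percentages are the share of replicates significant at 5%; they are false positives where the true HR is 1.

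| True HR | ASPP / control follow-up up to (years) | Logistic OR | Cox HR |
|---|---|---|---|
| 1 | 10.1 / 10.1 | 1.01 (5.5%) | 1.01 (4.2%) |
| 1 | 7 / 10.1 | 0.69 (30%) | 1.00 (5%) |
| 1 | 10.1 / 5 | 2.07 (72%) | 1.00 (4.8%) |
| 0.6 | 10.1 / 10.1 | 0.58 (49%) | 0.59 (50%) |
| 0.6 | 10.1 / 5 | 1.24 (10%) | 0.60 (34%) |

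At 5% per year the ORs follow the same pattern (1.00, 0.67, 2.14, 0.58 and 1.21). Cox recovers the true value throughout. The OR does so only when follow-up is alike. For scale, the Sample size estimates section aims to detect a 40% risk reduction in recurrence.

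**4. Matching ignored in the Aim 1 case-control part.** Let p be the exposure prevalence among controls in a matching stratum. The prevalence among cases is OR·p / (1 − p + OR·p). Average both over the strata (weights 0.34, 0.33, 0.33) and form the crude OR. The prevalences are assumptions.

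Worked line, true OR 2.0, prevalences 10/30/50%:
- Cases by stratum: 0.182, 0.462, 0.667; weighted mean 0.434.
- Controls: weighted mean 0.298.
- Crude OR = (0.434/0.566) / (0.298/0.702) = 1.81.

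| Prevalence by stratum | True OR 2.0 becomes | True OR 1.45 becomes |
|---|---|---|
| 30/30/30% | 2.00 | 1.45 |
| 10/30/50% | 1.81 | 1.38 |
| 5/30/70% | 1.58 | 1.28 |

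This loss occurs only if the matching factors are absent from the model.

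**The case against.** Four arguments can be made for the plan.

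- **Time-to-event methods are planned.** A reader might infer that the study has no time-to-event analysis of recurrence. The text does not support that: Kaplan-Meier, log-rank and Cox are named, and Table 3 records the interval to recurrence, so Cox for recurrent stroke is a natural reading. This stands as far as it goes. Still, the only sentence that names the outcome gives it an OR, so the choice is unresolved.
- **The bias is conditional.** A reader might infer that the ORs are necessarily biased. They are not. All groups share one inclusion window and one set of call dates, and with equal follow-up the OR and HR nearly coincide (0.58 and 0.59 at a true HR of 0.6). The 4 versus 6 year contrast is an assumption. The one cue in the text, the recent stroke in the nonpregnant group, would shorten control follow-up and push the OR above 1, not below. What stands against the plan is that nothing in it keeps follow-up equal.
- **The wide range describes round 1.** Women reached at round 3 would have roughly 6 to 16 years. That narrows the relative spread but does not equalise time at risk.
- **The regression is multivariable.** Age and hypertension are baseline variables, and entering them would largely remove the attenuation. This is fair, and a covariate list is ordinary detail for the full plan. It is also wrong to say that chi-square, t or rank tests bias an OR, since they estimate none; there only the p-values are in question. Predictors of prognosis studied within ASPP patients alone involve no pairs.

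**Conclusion.** The concern holds in a limited form. The article assigns a time-blind estimator to the Aim 2 primary outcome while follow-up at round 1 varies from about 1 day to 10.2 years, and does not say whether that OR or a Cox HR is the answer. The OR is trustworthy only if follow-up is distributed alike in the groups, which the design permits but does not secure. Under an assumed 2% per year, plausible imbalances give ORs from 0.65 to 1.53 where the true effect is nil; at the low end this is close in size to the effect sought. The actual direction and size cannot be known from the article.

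The matching issue is smaller. In Aim 1, a true OR of 2.0 would be estimated at 1.58 to 2.00 under the assumed prevalences, and only if the matching factors are omitted. In Aim 2 the consequence is mainly for standard errors.

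Two stronger remedies a reader might infer are not needed. Index-date matching is largely unnecessary once follow-up is censored properly, and logistic regression of recurrence need not be banned if it is confined to a fixed horizon.

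**What to change.** 1. **Aim 2.** State that Cox regression from the index-stroke date, censored at last contact or death, is the primary analysis of recurrent stroke, with pairs handled by robust variance or stratification.
2. **Logistic OR for recurrence.** Drop it, or keep it as secondary at a fixed horizon among women followed that long.
3. **mRS/EQ-5D at follow-up.** Include time since stroke in the model.
4. **Aim 1 risk factors.** Use conditional logistic regression, or unconditional logistic regression with age and hypertension history forced in.

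The cost is a few sentences in the Statistical analysis section. Admission dates (Table 2) and the interval to recurrence (Table 3) are already to be collected, so neither recruitment nor the matching scheme changes.

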## Discussion

ASPP is a rare yet severe complication in pregnant and postpartum women, significantly impacting their prognosis and survival. Several studies have demonstrated the incidence rate, risk factors, and treatment trends associated with ASPP [16, 17]. However, due to the rarity of this condition, prior research has relied on national healthcare databases and the ICD-10-CM coding to extract variables and outcomes, which inevitably limits the collection of detailed information necessary for a comprehensive investigation. Therefore, data from a patient-level cohort is essential for addressing significant unresolved clinical issues related to ASPP.

The ASPP is a retrospective, observational, nationwide, multicenter research project aimed at exploring both the short-term and long-term outcomes of the offspring of ASPP patients and their future development. This study has several notable strengths. First, it benefits from access to detailed patient-level data, including baseline characteristics and outcomes for both the women and their offspring, such as stroke severity, neuroimaging characteristics, management strategies during hospitalization, and Apgar and ASQ-3 scores of the offspring. Second, this study does not rely on the ICD-10-CM coding and can thus avoid coding errors, such as misclassification and underreporting. Third, it is capable of collecting long-term recovery outcomes for ASPP patients, an achievement not previously attained in studies on this subject. Fourth, both Apgar and ASQ-3 scores will be collected to evaluate the short-term and long-term impacts of ASPP on offspring. The results in this regard will aid physicians in informing parents about the potential effects of ASPP on the future development of their children. Consequently, this study may provide evidence for the comprehensive management of ASPP and inform the long-term prognosis for both ASPP patients and their offspring.

It is particularly important to emphasize that the etiology of stroke in ASPP patients is diverse, with a significant impact from pregnancy-related hypercoagulability on stroke risk [18]. During pregnancy, hormonal fluctuations, especially increases in estrogen and progesterone, may lead to changes in coagulation mechanisms, thereby increasing the risk of thrombosis [19]. This physiological change may not only result in venous thrombosis during pregnancy but may also trigger arterial thrombosis and other cardiovascular events. Specifically, risk factors for pregnancy-related hypercoagulability include previous thrombotic events, obesity, advanced maternal age, and family history [20]. Hormonal changes during pregnancy may also affect the occurrence or rupture of intracranial aneurysms, thereby increasing the risk of stroke [17]. Preexisting cerebrovascular abnormalities, such as arteriovenous malformations, moyamoya disease, or untreated aneurysms, may further increase this risk [21]. These structural abnormalities usually require specialized management strategies, such as endovascular intervention versus conservative monitoring, which directly affect recurrence rates and long-term functional outcomes. This study included detailed neuroimaging reviews to document these potential diseases, enabling subgroup analyses of their impact on secondary prevention effectiveness and recurrence patterns during follow-up.

Other causes of stroke must also be considered, such as arterial dissection. This condition may be more common in young women, especially after childbirth, due to potential tears in the vascular intima [22]. Cardioembolic strokes can result from atrial fibrillation, valvular heart disease, or other heart issues. These conditions may be more frequent during pregnancy because of physiological changes and increased heart strain [23]. The complexity of these causes highlights the need for thorough risk assessment in pregnant women to identify and manage potential stroke risk factors.

In addition, managing ASPP requires individualized treatment plans based on the specific causes. When dealing with hypercoagulability, it is important to carefully consider the timing and choice of anticoagulant therapy to minimize risks to both the mother and fetus. Early neuroimaging assessments are also crucial in stroke management, as they help identify the location and nature of thrombi and guide treatment decisions.

The findings of this study should be interpreted within the context of potential limitations. Firstly, this is a retrospective study, which is subject to several inherent biases, such as recall and information bias, potentially jeopardizing its validity. Secondly, follow-up via telephone interviews may lead to a high dropout rate. Thirdly, concerns among ASPP patients regarding the privacy of their offspring’s information may result in a significant number being unwilling to cooperate, leading to selection bias. To address these issues, expanding the sample size by including more centers would be an effective solution for achieving statistical validity. Finally, although this study focuses on the Chinese population and mainly includes the Han ethnic group as the primary ethnic cohort, it employs two methodological measures, geographical heterogeneity and biological consistency, to ensure the generalizability of the research findings. The study included 22 provinces representing different socio-economic and medical resource conditions to ensure geographical heterogeneity. According to previous national studies, in the Chinese population, the key risk factors for ASPP, such as hypertension and coagulation dysfunction, show minimal differences across different ethnic groups, suggesting that the study subjects have biological consistency [24, 25].

## Conclusions

The ASPP study is a nationwide, multicenter, patient-level investigation that retrospectively encompasses ASPP patients and non-ASPP participants from 36 centers across China. This study aims to provide comprehensive information on the risk factors associated with ASPP, as well as its short-term and long-term prognoses and the risk of recurrent stroke, particularly during subsequent pregnancies. Furthermore, it will be the first study to explore whether this severe complication during pregnancy affects the future development of offspring.

## Data Availability

Not applicable.

## Abbreviations

ASPP: Acute stroke in pregnancy and puerperium
mRS: Modified Rankin Scale
EQ-5D: EuroQol five dimensions questionnaire
ASQ-3: Age & Stages Questionnaires, Third Edition
